## Assignment of interventions: masking

### Who will be masked {17a}

Post-intervention allocation, there is no masking as households and project participants in clusters assigned to intervention or control will be aware of their allocation given the nature of the intervention.

### Procedure for unmasking if needed {17b}

Not applicable.

## Data collection and management

### Plans for assessment and collection of outcomes {18a}

Baseline data is collected for the impact evaluation (November 2020), before the DIG programme starts; after the DIG programme ends following 18 months of implementation, data is collected for the first endline from households with people with disabilities (July 2022), and for the second endline from all households and participants (October 2023). Data is collected for the baseline and endlines using questionnaires that have been piloted prior to use. Questionnaires are administered by experienced and trained data collectors, overseen by BIGD/IERC, to members of selected households in both the control and intervention arms (see Table 3 for questionnaire domains, full questionnaires available in Supplemental file 2). One questionnaire refers to features of the household and should be completed by the female head of household. Another questionnaire refers to the person with disabilities and should be completed by this person, if different to the female head of household. The female head of household survey includes a tool that has been adapted and verified for the Ugandan context to measure per-capita monthly expenditure at the household level. The survey for the person with disabilities collects disability-related information and was adapted from the World Health Organization’s Model Disability Survey [12].

**Table 3 Tab3:** Questionnaire domains

**Female head of household**	**Person with disability**
□ Identification and household characteristics □ Household welfare and assets □ Household expenditure □ Household agriculture, livelihoods, and other income-generating activities □ Household loans and savings □ Household use of assistance □ Food security □ Vulnerability to shocks □ Health of household members	□ Self-rated health / perceived well-being; self-stigma/negative attitudes □ Quality of life □ Household decision making □ Participation □ Attitudes & behaviour of others □ Environmental factors □ Personal assistance and assistive devices

The process evaluation uses data from the impact evaluation in conjunction with other data sources. This includes programme monitoring data collected by BRAC Uganda at the branch and national level, such as records of asset transfer timings, number of household visits (and by whom), and other project activities. A compliance survey conducted by BRAC Uganda as part of their programme monitoring activities is conducted halfway through programme implementation (July 2021), this will inform the level of exposure to the intervention among project participants. This is complemented by questions in the endline surveys on exposure to intervention components. Qualitative interviews with the project staff (approximately 10) and project participants (approximately 30; 15 in each arm, 10 with disabilities and 5 without) are conducted at the end of the project to address domains such as fidelity, adaption, reach, mediators, unintended consequences, and context of programme implementation, and to further understand participant responses to the intervention. The endline surveys also provide data for the process evaluation regarding factors expected to be on the causal pathway, and contextual factors. Further information on the process evaluation domains can be found in Supplemental file 3.

### Plans to promote participant retention and complete follow-up {18b}

Consent and data collection procedures are adapted to support the participation of people with different impairments (e.g. sign language for participants with profound hearing impairments and knowledge of a standard sign language). Interviews take 60–120 min per visit and could be tiring for participants. To compensate for this fatigue, participants are offered a small token (bar of soap or a kilogramme of sugar) at the end of the interview as an appreciation. Participants are given the opportunity to stop at any time if they become fatigued and would no longer like to continue participating.

### Data management {19}

Quantitative data collection is conducted by IERC and BIGD, and qualitative data collection for the process evaluation done by Makerere University. Qualitative data collected through interviews with beneficiaries and key informants are audio recorded, then transcribed and translated into English. Audio recordings and transcripts are securely stored by the head of the qualitative evaluation team. Quantitative data, collected through the household surveys, is collected electronically using SurveyCTO (Dobility, Inc. Cambridge, MA, USA), where all data is password protected on devices and servers. Once BIGD have cleaned and ensured the data is anonymized, data is shared with LSHTM in the UK using a secure data transfer protocol, where it is securely stored on LSHTM servers.

### Confidentiality {27}

All study staff undergo ethics training and sign a confidentiality agreement. The research team ensures that all research data collected are anonymised using unique identification numbers.

### Plans for collection, laboratory evaluation and storage of biological specimens for genetic or molecular analysis in this trial/future use {33}

Not applicable, as no biological specimens collected.

## Statistical methods

### Statistical methods for primary and secondary outcomes {20a}

For basic description, we will report the mean and standard deviation (or median and interquartile range) for continuous variable and the number and percentage for categorical variables, by intervention status (yes or no), and by data wave (baseline vs follow-up). We will test the balance of the covariates by *t*-test (or Mann Whitney *U* test) for continuous variables and by chi-square test for any categorical variables. Covariates include socio-demographic factors (e.g., age, sex), as well as any other factors likely to affect the implementation of the intervention.

Data will be fitted with multi-level linear regression to test the effect of the intervention, with the difference of the primary or secondary outcomes between follow-up and baseline as the outcome, and intervention status as the exposure, controlling for potential imbalance in covariates at baseline. To account for the data structure, we will consider the random intercept and random slope for exposure at the level of district and pair indicators. To address multiplicity concerns the Bonferroni Correction or Bayesian modelling approaches will be applied. The model’s adequacy will be assessed through residual plots, with log transformations of variables considered if residuals are not randomly distributed. All analysis will be conducted in Stata and R. We will report the estimation as coefficient for continuous outcome and OR for binary outcome, as well as their 95% confidence interval (CI). *P* value < 0.05 will the level of statistical significance.

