### Trial design {8}

The overall effect of the intervention is estimated using a two-arm, parallel group, longitudinal, pair-matched cluster-randomised controlled superiority trial design. Clusters are defined as villages with 10–75 eligible households, within which households act as the observational unit (see ‘Eligibility criteria {10}’ section for further details).

The DIG programme has identified more than 11,000 eligible households, but only has funding to reach 2700 households under the programme. Randomisation is therefore an equitable way to select households for inclusion. It is also not yet clear that the intervention is effective for people with disabilities and their families. Cluster randomisation was chosen in part because of the nature of the DIG programme, which includes components delivered at the village level.

After random allocation of villages into intervention and control arms, but prior to implementation of the intervention, a baseline survey at household level is conducted (November 2020). The DIG programme is then implemented for 18 months from December 2020 to June 2022. Two endline household surveys are undertaken—the first in July 2022 for participants with a disability to determine the effects of DIG at programme end (endline 1); and a second one in October 2023 for all participants (endline 2), inclusive of participants with disabilities, to assess the longer-term differential effects of the DIG programme between households with and without disabilities.

This work is complemented by a process evaluation to further understand implementation of the DIG programme. The process evaluation is guided by theoretical considerations, such as What underlying theory are we testing with this intervention? What is the theory underlying the design of the graduation programme? And what is the theory underlying the adaptations to make them inclusive? These considerations ground the process evaluation in the relevant wider literature, and support generalisability to future intervention designs that draw on similar theories. To facilitate consideration of theory, an unambiguous articulation of project theory as supposed by the delivery team is developed iteratively in the form of a directed acyclic graph (DAG), based on the theory of change and using set rules for specifying how change is expected to happen.

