Available data from the screening and verification visits informed the estimated total number of clusters that would be needed to reach 5400 eligible households. During the screening and verification process, BRAC Uganda found that approximately 25% of project participants were people with disabilities, and as such it was expected that the trial would include 675 people with disabilities in each arm. The distribution of eligible households per village was used to simulate the trial, 185 villages sampled with replacement from the verified villages gave approximately 5400 research participants in a simulated trial. A value of 0.8 was used from a recent evaluation of the graduation programme in Ghana for the standard deviation of the distribution of the normalised per-capita expenditure at baseline [10]. Since the degree of clustering in the outcome was unknown, the intraclass correlation coefficient (ICC) was allowed to vary between 0.05 and 0.3. The estimated between-village variation in mean level of the outcome at baseline and individual-level outcomes were drawn from the village-level means with a constant within-village variance. The endline results were generated using the simulated baseline data and a covariance matrix with a pre-post correlation of either 0.4, 0.6, or 0.8. The 185 clusters were pair-matched by the number of people with disabilities and a constant intervention effect was applied to the clusters allocated to the intervention arm. The intervention effects ranged from a difference between the intervention and control arms in the mean per-capita expenditure of zero standard deviations of the baseline per-capita expenditure, to 0.2 standard deviations, which is as high as the largest effects on per-capita expenditure observed in previous trials [1]. Multi-level linear regression was used to estimate the effects, controlling for baseline per-capita expenditure, accounting for clustering with a village-level random effect, and for the randomised design with fixed-effect for the pairs.

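### The planned change-score analysis is not the baseline-adjusted model behind the precision claim, and as worded it cannot give the promised odds ratio

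*Protocol article*

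**What the plan says.** **Analysis.** Statistical methods {20a} states: "Data will be fitted with multi-level linear regression to test the effect of the intervention". The regression is run "with the difference of the primary or secondary outcomes between follow-up and baseline as the outcome", with intervention status as the exposure, "controlling for potential imbalance in covariates at baseline". On covariates it says: "Covariates include socio-demographic factors (e.g., age, sex), as well as any other factors likely to affect the implementation of the intervention". The baseline value of the outcome is not mentioned.

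The same section has two further steps. Model adequacy is judged from residual plots, "with log transformations of variables considered if residuals are not randomly distributed". On reporting it says: "We will report the estimation as coefficient for continuous outcome and OR for binary outcome". No logistic model is named. Outcomes {12} includes a binary outcome, household poverty status against a line of US$1.90 per day.

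**Precision.** Sample size {14} simulates endline from baseline with a pre-post correlation of 0.4, 0.6 or 0.8 and an ICC from 0.05 to 0.3. It estimates the effect with a model "controlling for baseline per-capita expenditure, accounting for clustering with a village-level random effect" and fixed effects for the matched pairs. From this it concludes that a true effect of 0.1 baseline standard deviations would be detected under conservative assumptions.

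**Timing.** Trial design {8} places the baseline survey after allocation: "After random allocation of villages into intervention and control arms, but prior to implementation of the intervention, a baseline survey".

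**The concern.** The document describes two models for the primary outcome. One regresses endline on baseline and supports the 0.1 SD claim. The other subtracts baseline and is the one to be run. Subtraction fixes the slope on baseline at 1, whereas adjustment estimates it. When the pre-post correlation is modest, a slope of 1 over-corrects and adds noise. The study's size is fixed by programme funding, so precision given up in the analysis cannot be bought back by recruiting more households.

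The wording also applies one linear model of a difference to primary and secondary outcomes alike, yet promises an odds ratio for binary ones. And it leaves the scale of the primary outcome, levels or logs, to be settled after residuals have been seen.

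**Working it through.** **Inputs, all from Sample size {14}:** pre-post correlation r = 0.4, 0.6, 0.8; ICC 0.05 to 0.3; 675 people with disabilities per arm; 185 clusters; target effect 0.1 baseline SD. The 5% level is from {20a}, taken as two-sided.

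**Assumptions:** outcome variance of 1 at both waves, the same r at village and household level, and no baseline outcome among the covariates.

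**Step 1: residual variance.** Change score: 2(1 − r). Baseline-adjusted: 1 − r². Relative efficiency of the change score: (1 − r²) / [2(1 − r)] = (1 + r)/2.

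| r | Change score | Baseline-adjusted | Ignoring baseline | Relative efficiency | Information lost |
|---|---|---|---|---|---|
| 0.4 | 1.20 | 0.84 | 1.00 | 0.70 | 30% |
| 0.6 | 0.80 | 0.64 | 1.00 | 0.80 | 20% |
| 0.8 | 0.40 | 0.36 | 1.00 | 0.90 | 10% |

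At r = 0.4 the change score (1.20) is worse than using endline alone (1.00).

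**Step 2: the plan's own figure.** The protocol gives no numerical power and its precision figure is not shown, so the 0.1 SD statement cannot be matched exactly. The nearest check is r = 0.4 without clustering.
- Baseline-adjusted: SE = √(2 × 0.84/675) = 0.0499 and 1.96 × 0.0499 = 0.098, so an interval centred on 0.1 just excludes zero.
- Change score: SE = √(2 × 1.2/675) = 0.0596 and 1.96 × 0.0596 = 0.117, so it does not.

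**Step 3: power at 0.1 SD, ICC 0.05.** Cluster size m = 1350/185 = 7.3; design effect 1 + (7.3 − 1) × 0.05 = 1.31; SE = √(2 × variance × 1.31/675).

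| r | Baseline-adjusted | Change score |
|---|---|---|
| 0.4 | 42% | 31% |
| 0.6 | 52% | 43% |
| 0.8 | 76% | 72% |

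These figures omit the pair matching and pair effects in {14}. They compare the two models and do not reproduce the protocol's own simulation.

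**Step 4: does the loss survive other correlation structures?** A two-level simulation used 184 clusters, a village random effect, no pair terms and 400 runs per scenario. It compared the change score with adjustment for household baseline only.
- Same correlation at both levels: efficiency 0.69 to 0.91, in line with Step 1.
- Village-level correlation set to 1, m = 7.3: efficiency 0.87 to 0.94 at ICC 0.05, and 1.11 to 1.73 at ICC 0.3.
- Village-level correlation set to 1, m = 29.2 (5400/185, all households): 1.07 to 1.28 at ICC 0.05, and 2.31 to 5.65 at ICC 0.3.

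With perfectly stable village levels, subtraction removes the village effect, which adjustment for household baseline alone does not do.

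**Step 5: baseline as covariate.** If Y1 − Y0 = a + bT + cY0, then Y1 = a + bT + (c + 1)Y0. The treatment effect b is the same, so the loss is zero.

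**Step 6: binary outcome.** Poverty status is 0 or 1 at each wave, so its difference is −1, 0 or 1. A linear model of that gives a mean difference in change, not an odds ratio.

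**The case against.** The strongest reply is that the loss is conditional. The covariate list in {20a} is open-ended, so baseline expenditure may be meant to be in it, and Step 5 shows that the two approaches then coincide. Even if it is left out, Step 4 shows that the change score can be the more precise model at an ICC inside the protocol's own range. Both points stand. A reader might infer that 10 to 30% of the information is certainly thrown away, but the document does not settle that. It does settle that two models are described and that the baseline outcome is named in only one of them. The reversal also depends on village stability beyond the single correlation that {14} states. Entering the cluster-mean baseline answers it, because both slopes are then estimated and not fixed at 1.

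A reader might also infer that the log step is impossible because a change can be negative. The text speaks of variables, and expenditure can be logged at each wave before differencing. What remains is that the scale is ambiguous and would be chosen from residuals.

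On the odds ratio, a condensed article may leave the binary model to the analysis plan, and promising an odds ratio implies a logistic model. That makes it a drafting inconsistency in a secondary outcome, not evidence about the primary analysis.

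Finally, baseline is surveyed after allocation that is neither concealed nor masked, and a reader might infer bias. No anticipation effect, and no direction for one, is documented. As a purely hypothetical case, a 0.05 SD shift at baseline would move the change-score estimate by 0.05 SD and the baseline-adjusted one by about r × 0.05 = 0.02 SD at r = 0.4. The risk comes from the survey's timing, and adjustment reduces it without removing it. Without anticipation, the change score is unbiased under randomisation.

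**Conclusion.** The point holds in limited form. The analysis in {20a} is not the model on which the precision statement in {14} rests, and the two should be reconciled. If the baseline outcome is not adjusted for, with equal variances and one correlation at both levels, the cost is up to about 30% of the information at r = 0.4, 20% at 0.6 and 10% at 0.8. Standard errors are then larger by 19.5%, 11.8% and 5.4%. The cost is nil if baseline is a covariate. Against adjustment for household baseline alone, it may shrink or reverse where village levels are stable and the ICC is high; in the simulation with about 29 households per cluster it reversed even at ICC 0.05.

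The odds-ratio wording is inconsistent as it stands. The choice of scale should not wait for residual plots. The documents do not support a claim that the log step cannot be done, that the estimate is biased, or that anticipation occurred. Whether the trial has enough power at 0.1 SD is a separate question.

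**What to change.** - **Primary and other continuous outcomes:** make the endline value the outcome, with the baseline value of the same outcome as a covariate, preferably both the household value and the cluster mean. Carry over the village random effect and pair terms from {14}, so that the analysis and the precision statement use the same model.
- **Poverty status:** name a mixed logistic model of endline status adjusted for baseline status, reported as an odds ratio.
- **Scale:** state before analysis whether expenditure is analysed in levels or logs. If logs, regress log endline on log baseline. The other scale can serve as a sensitivity analysis.
- **Timing of baseline:** acknowledge that it was surveyed after unmasked allocation, and that adjustment limits a possible anticipation effect only in part.

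The cost is a change of wording. All the data needed are already part of the planned surveys.

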The results from the simulated analyses are shown in Fig. 3. The darker CIs correspond to scenarios with higher ICCs. Estimates were precise when the pre-post correlation was high (right-hand panel), and sufficiently precise to exclude the null with a low correlation and true effect of a difference between the arms of 0.1 standard deviation of per-capita expenditure at baseline (left-hand panel). Under conservative assumptions, we would reject the null hypothesis at conventional levels (*p* < 0.05) if the true effect of the intervention on per-capita expenditure was at least 0.1 standard deviations of the baseline distribution. This effect size is similar in magnitude to the overall effect on per-capita expenditure found in trials of the original (non-inclusive) version of the programme [1]; therefore, this trial would have sufficient power to detect an effect if the adaptations of the intervention for people with disabilities worked such that the effect was as strong as it had been for people without disabilities.

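### Households with a person with disabilities are measured at two endlines, but the stated model has a single follow-up and so gives no interval for whether the effect changes between them

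*Protocol article*

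**What the plan says.** Trial design {8} describes a "two-arm, parallel group, longitudinal, pair-matched cluster-randomised controlled superiority trial design". Endline 1, in July 2022, covers participants with a disability and is meant to show the effect at programme end. Endline 2 is "a second one in October 2023 for all participants (endline 2), inclusive of participants with disabilities", and its stated purpose is the longer-term differential effect between households with and without disabilities. Table 1 and section {18a} confirm that households with a person with disabilities are surveyed at baseline and at both endlines.

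Statistical methods {20a} recognises two data waves only, baseline and follow-up. The model is a multi-level linear regression "with the difference of the primary or secondary outcomes between follow-up and baseline as the outcome", with intervention status as the exposure and adjustment for imbalanced covariates. A random intercept and a random slope are considered at district and pair level. The text has no wave term, no arm-by-wave term, no household term and no randomised-cluster term. It does not say which endline is the follow-up, or whether the model is fitted once per endline.

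Section {20c} adds imputation, as a sensitivity analysis, for participants who withdraw consent. The imputation variables are not named. The simulation model in Sample size {14} differs from {20a}: it controls for baseline expenditure and has a village random effect, with one endline.

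**The concern.** The data have three waves and the stated model has two. Fitted separately at each endline, the model yields two correlated estimates in the same households but not their covariance, so their difference has no standard error. Readers of a programme that aims at sustainable livelihoods will still ask whether the effect lasted. With only two separate results, the easy answer is to compare p-values: significant at endline 1, not significant at endline 2, therefore faded. That comparison is not a test of change, and the error can occur whichever endline is primary.

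A lesser consequence is that, in the main analysis, a household seen at endline 1 and lost by endline 2 adds nothing to the endline 2 estimate, although its endline 1 value carries information.

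**Working it through.** The plan gives no figure for the change in effect between endlines, so there is none to reproduce. Its target of 0.1 SD for a single endline is used below only as a yardstick.

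**Inputs from the article (Sample size {14}):** 675 people with disabilities per arm; 185 clusters; ICC 0.05 to 0.3; pre-post correlation 0.4, 0.6 or 0.8. Two-sided 5% is inferred from the 95% CI in {20a}.

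**Assumptions:** one common correlation *r* across all three waves, equal variances, the same design effect for every contrast, and 80 to 90% retained at endline 2. The article gives neither an endline-to-endline correlation nor attrition.

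**1. Correlation between the two effect estimates.**
- Change scores from a common baseline: covariance 1 − *r*, variance 2(1 − *r*), so ρ = 0.5 for any *r*.
- Baseline-adjusted: covariance *r* − *r*², variance 1 − *r*², so ρ = *r*/(1 + *r*) = 0.29, 0.38, 0.44 for *r* = 0.4, 0.6, 0.8.

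**2. SE of the change in effect, relative to treating the estimates as independent:** √(1 − ρ).
- Change scores: √0.5 = 0.71.
- Baseline-adjusted: 0.85, 0.79, 0.75.

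**3. Absolute SE with full follow-up.** There are 1350/185 = 7.3 people per cluster, so the design effect is 1 + 6.3 × ICC = 1.315 at ICC 0.05 and 2.89 at ICC 0.3. The SE is √[(2/675) × design effect × 2(1 − *r*)].

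| ICC | *r* | SE of change (SD units) | Two change-score fits treated as independent | 95% half-width (1.96 × SE of change) |
|---|---|---|---|---|
| 0.05 | 0.4 | 0.068 | 0.097 | 0.134 |
| 0.05 | 0.8 | 0.040 | 0.056 | 0.077 |
| 0.3 | 0.4 | 0.101 | 0.143 | 0.199 |
| 0.3 | 0.8 | 0.059 | 0.083 | 0.115 |

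Under a common *r*, endline 2 minus endline 1 is uncorrelated with baseline. The SE of the change is therefore the same for change scores and for baseline adjustment; only the comparator differs.

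**4. How often side-by-side p-values mislead.** Take a true effect of 0.1 SD at both endlines, change-score fits (ρ = 0.5) and full follow-up. Over ICC 0.05 to 0.3 and *r* 0.4 to 0.8, bivariate normal probabilities give exactly one significant endline in 20 to 33% of trials. Significance at endline 1 only, an apparent fade-out that is false, occurs in 10 to 16%.

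**5. Gain from using endline 1 when endline 2 is missing at random.** With retained share *a*, the variance ratio of joint to separate analysis is (1 − ρ²) + *a*ρ², a reduction of (1 − *a*)ρ².
- Baseline-adjusted: from 0.1 × 0.29² = 0.8% to 0.2 × 0.44² = 4.0%.
- Change scores: from 0.1 × 0.25 = 2.5% to 0.2 × 0.25 = 5.0%.

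**6. Sensitivity to the common-correlation assumption (change scores).**
- Pre-post 0.4 and endline-to-endline 0.8: ρ = (0.8 − 0.4 − 0.4 + 1)/1.2 = 0.83. The SE ratio falls to 0.41, and the variance gain at 80% retained rises to 0.2 × 0.83² = 14%.
- Pre-post 0.8 and endline-to-endline 0.4: ρ = (0.4 − 0.8 − 0.8 + 1)/0.4 = −0.5. The SE ratio is √1.5 = 1.22, so independence would understate the SE.

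An assumption of independence can therefore err in either direction.

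**The case against.** The strongest reply is that no promised result is missing. Objectives {7} asks for the effect in people with disabilities and for its difference from people without disabilities. It does not ask for the change in effect between endlines. Trial design {8} gives each endline its own purpose, and a per-endline fit is a valid estimate at each under full follow-up. This stands, and it limits the point to an improvement.

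A reader might infer that the trial can never obtain a standard error for persistence. The article does not support that: {20a} is silent on a joint model and does not rule one out, and the same regression applied to endline 2 minus endline 1 would supply the standard error. An analysis plan that is not shown may do so. Nor does any section plan to judge persistence by comparing p-values; that risk lies in how readers would use two separate results.

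A reader might also infer that endline 1 data are wholly discarded for households lost by endline 2. That holds for the main model only, since the sensitivity imputation in {20c} could draw on them.

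Larger effects on precision follow if raw correlations of 0.4 to 0.8 are used directly as ρ. Under one common correlation that is the wrong quantity, because the estimates are change scores or baseline-adjusted.

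What the reply does not remove is that {20a} does specify an outcome, an exposure and random effects, and that specification fits two waves where the design has three.

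**Conclusion.** The point holds as a modest one. As written, the model gives no interval for the endline 2 minus endline 1 change in effect among households with a person with disabilities, and its main analysis ignores endline 1 when endline 2 is missing.

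The main benefit of a joint model is a valid contrast. Its SE is about 0.71 to 0.85 times the independence figure under a common correlation of 0.4 to 0.8. The precision gain at endline 2 is small, about 1 to 5% of the variance with 80 to 90% retained. Both ranges rest on correlations and retention that the article does not give, and they widen if endline-to-endline and pre-post correlations differ.

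The contrast will not be sharp. Its 95% half-width is about 0.08 to 0.20 SD against a target effect of 0.1 SD, so in many scenarios the honest statement will be that persistence is uncertain. Two separate p-values would hide that.

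**What to change.** For households with a person with disabilities, specify one mixed model with both endlines as outcomes, arm-by-wave terms, the baseline value as covariate in place of the change score, and random effects for household and randomised cluster. Baseline adjustment and a cluster-level random effect would also bring the analysis closer to the model simulated in Sample size {14}. Report the effect at each endline and the endline 2 minus endline 1 change in effect with its 95% CI. State that any claim of fade-out or persistence rests on that interval. Say in {20a} which endline each use of follow-up refers to.

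If only the contrast is wanted, regressing the endline 2 minus endline 1 difference on arm, with the same design terms, is a simpler equivalent under full follow-up.

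The cost is a few sentences of analysis-plan wording and one extra model, with no new data. The downside is that the joint model relies on endline 2 values being missing at random given baseline and endline 1.
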